### Statistical analysis

All quantitative analyses will be conducted using Stata (v18, StataCorp, College Station, Texas, USA) and R (v4.5, R foundation for Statistical Computing, Vienna, Austria). Analyses will be both descriptive and inferential, using multivariable regression models with appropriate adjustments for confounders. Participant recruitment, follow-up and exclusions will be illustrated using a flow diagram, in line with the Strengthening the Reporting of Observational Studies in Epidemiology (STROBE) guidelines for observational studies. Descriptive statistics will be used to summarise baseline characteristics, means and SD for normally distributed continuous variables, medians and IQRs for skewed distributions, and frequencies and percentages for categorical variables. The characteristics of EMaBS participants included in EMaBS@21 will be compared with the characteristics of EMaBS participants not included in EMaBS@21 to determine how generalisable the findings are to the originally recruited cohort of participants. Characteristics to be compared will be those collected during pregnancy at the original EMaBS enrolment at delivery and during childhood (for those followed to this period).

#### Objective 1: to determine the effect of early-life exposures on physiological determinants of CVDs measured in young Ugandan adults

We will use regression analysis to assess associations with our primary exposures of interest—namely infections and growth/undernutrition—across specific life-course exposure periods. For continuous outcomes, we will use linear regression models to assess associations between each exposure and each outcome, adjusting for confounders. For binary outcomes, logistic regression models will be used to determine the effect of each exposure on the outcome, adjusting for confounders. First, exposures will be modelled individually at each time point to examine cross-sectional associations with the outcomes. Where exposure data have been collected repeatedly over time, such as for malaria and *S. mansoni* infections, we will explore trajectories of exposure and their relationships with study outcomes using latent class or trajectory analysis. Repeated binary measures will also be analysed as time-varying covariates in mixed-effects models.

Additionally, we will leverage longitudinal data collected on the same outcome measures at age 10–11 years, which will also enable the inclusion of participants with some missing time-point data. Causal modelling approaches will be used to obtain unbiased estimates of the average causal effect of each early-life exposure on each outcome, adjusting for confounders. For each exposure-outcome relationship, we will construct directed acyclic graphs to identify the minimal sufficient set of confounders. Inverse probability weighting will be applied to create a pseudo-population in which exposure is independent of measured confounders, thereby enabling adjustment for selection bias due to differential loss to follow-up or missing outcome data. We will also explore secondary exposures of interest, including selected genetic variants from existing whole-genome data that have been linked to CVD risk in other populations.

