### Study populations and recruitment

The study will be conducted among EMaBS participants, who will be contacted and invited to participate in Entebbe Mother and Baby Study at 21 years (EMaBS@21). The EMaBS birth cohort began life as a randomised controlled trial aimed at investigating the impact of anthelmintic treatment during pregnancy and early childhood on responses to immunisations, incidence of infectious and allergy-related diseases, and growth and nutrition (ISRCTN32849447).^9^ A total of 2345 documented live-born children were recorded in the cohort between 2003 and 2006. EMaBS cohort attrition due to mortality or loss to follow-up was highest during the first 5 years of life (27% in infancy, 45% from birth to 5 years) and has stabilised at an average of ~2% per year since then. For example, 1270 participants were seen at age 5 years, 1119 at age 10–11 years and 976 were seen at the EMaBS clinic when aged 15–18 years. In April 2023, we undertook a cohort census in concert with a dissemination open day. A total of about 1500 cohort participants, over half of whom attended the open day, have provided comprehensive location and contact details and expressed willingness to be contacted to take part in future waves of data collection. We will use a census-based sampling approach for this study, that is, we plan to sample as many EMaBS participants as are available and meet the eligibility criteria within the recruitment time frame.

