### Objective 3: investigate nutritional and metabolic pathways through which early-life exposures may influence physiological determinants of CVDs

We will focus on both nutritional and metabolomics pathways. We will examine whether early-life growth influences micronutrient levels before age 5 years and whether these, alongside inflammation biomarkers, are associated with physiological risk markers at age 21 years. For metabolomics, we will analyse samples from individuals at the extremes of phenotypic expression. Metabolites will be identified and quantified using Progenesis QI software (Waters Corporation, Milford, MA, USA), and pathway-level analyses will be conducted using Integrated Molecular Pathway Level Analysis (IMPaLA). We will explore how early-life metabolic profiles relate to profiles at age 21 years and to extremes in exposure (eg, repeated *S. mansoni* infection vs none) and outcomes (eg, high vs low blood pressure). Causal mediation analysis will estimate both direct and indirect effects using a counterfactual framework, accounting for multiple mediators and applying sensitivity analyses to evaluate robustness to potential violations of confounding assumptions and measurement error.

Missing data will be assessed and handled using multiple imputation by chained equations when over 5% of data are missing for key variables, where applicable. Where repeated-measures data are available and intermediate data points are missing, we will use multiple imputation by chained equations to impute missing values, leveraging information from previous and subsequent measurements as well as relevant covariates. Therefore, imputations will include outcome variables and predictors of missingness, with 50 imputed datasets combined using Rubin’s rules.

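### The weights described for Objective 1 balance confounders; they do not, as the protocol says, also adjust for selection through loss to follow-up, so the causal estimates may remain biased

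*Protocol article*

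**What the plan says.** The protocol article, Statistical analysis, Objective 1, sets the aim of the causal work: "Causal modelling approaches will be used to obtain unbiased estimates of the average causal effect of each early-life exposure on each outcome". The covariates are to come from causal diagrams: "we will construct directed acyclic graphs to identify the minimal sufficient set of confounders". The weighting is then described in one sentence, and its result is put this way: "exposure is independent of measured confounders, thereby enabling adjustment for selection bias due to differential loss to follow-up or missing outcome data". The first half gives the purpose, balance of exposure on confounders; the second half gives a claimed consequence, correction for selection. No model for attendance at 21, and no separate weight for it, appears in the article.

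Three other places bear on this.

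- Study populations and recruitment gives the starting point, "A total of 2345 documented live-born children were recorded in the cohort between 2003 and 2006", and the attrition from death or loss to follow-up: "27% in infancy, 45% from birth to 5 years".
- The missing-data paragraph, placed under Objective 3, plans multiple imputation by chained equations and says that "imputations will include outcome variables and predictors of missingness".
- The opening of Statistical analysis plans to compare cohort members who are and are not in the new round, on pregnancy, delivery and childhood characteristics.

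**The concern.** A weight that makes exposure independent of measured confounders is the inverse of the probability of the exposure received, given those confounders. It removes confounding among the people who are analysed. It carries no information on how those people came to be analysed.

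Selection is a different problem with a different model: the probability of being observed at 21, given the exposure and whatever predicts attendance. The variables this model needs most are causes of both dropout and outcome that are not causes of exposure. A minimal set chosen to block confounding has no reason to contain them. The word linking the two halves of the sentence makes selection adjustment a by-product of exposure balancing, so an analyst who follows the text would fit one model and report both problems as handled.

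The stake is Objective 1, the test of the primary hypothesis. Most of the attrition fell in the first five years, the period in which many of the infection, growth and nutrition exposures were measured. The article itself lists selection bias as a possible limitation.

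**Working it through.** **Step 1. The plan's own attrition figure.** Inputs from Study populations and recruitment: 2345 live births, 1270 seen at age 5. Attrition = 1 - 1270/2345 = 45.8%, against 45% stated. It agrees within one point, so the formula is the right one to carry forward.

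**Step 2. Share of live births not analysed at 21.**

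- Minimum target of 900 (Sample size determination): 1 - 900/2345 = 61.6%.
- 976 attend, as at 15–18 years: 1 - 976/2345 = 58.4%.
- All of about 1500 contactable members attend: 1 - 1500/2345 = 36.0%.

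These shares count deaths as well as losses. The article does not separate the two, so the share among survivors is lower by an amount that cannot be computed from it.

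**Step 3. What exposure weights do under different attendance patterns.** The article gives no data on what drives attendance, so every parameter here is an assumption.

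- One million subjects, 38.4% attending (900/2345).
- C is a confounder; the log-odds of exposure are -1 + 0.6C.
- L is a measured cause of the outcome but not of exposure.
- Outcome in mmHg = 115 + 2.0 × exposure + 2C + 3L + noise with SD 7.7.
- The exposure model uses C. The participation model, fitted in everyone, uses exposure, C, L and the product of exposure and L.

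Estimates of the true effect, 2.0 mmHg:

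| Attendance depends on (log-odds) | Exposure weights only | Exposure × participation weights |
|---|---|---|
| nothing (random) | 2.04 | 2.04 |
| C only (0.8) | 2.07 | 2.08 |
| exposure only (-1.0) | 2.04 | 2.02 |
| exposure (-1.0) and L (1.0) | 2.55 | 2.02 |
| exposure (-1.0), L (1.0) and their product (-1.5) | -0.45 | 2.03 |

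Departures of a few hundredths are simulation noise. The last two rows are not: the errors of exposure weights alone are 2.55 - 2.0 = 0.55 and -0.45 - 2.0 = -2.45 mmHg. In the last row attendance rises with L among the unexposed (1.0) and falls with L among the exposed (1.0 - 1.5 = -0.5). The two attending groups then differ in L, which the exposure model does not contain.

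**Step 4. A milder setting.** Assume a true effect of 0.25 SD, about 35% participation, and attendance depending on exposure and on a non-confounding cause of the outcome, with log-odds of 0.5 or 1.0 each. Exposure weights alone gave 0.264 and 0.292; adding participation weights gave 0.248 and 0.249. The errors are 0.264 - 0.25 = 0.014 SD and 0.292 - 0.25 = 0.042 SD. At the protocol's blood pressure SD of 8 to 10 mmHg these are 0.11 to 0.14 and 0.34 to 0.42 mmHg.

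**Step 5. A yardstick.** The smallest blood pressure difference in Table 1 is 1.8 mmHg. With 80% power at the 5% level this implies a standard error of about 1.8/(1.96 + 0.84) = 0.64 mmHg. The errors in Step 4 and the 0.55 in Step 3 are below one such standard error; the 2.45 is nearly four.

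**The case against.** **The bias is not certain.** Exposure weights alone did well in three of the five patterns, and in the milder setting the error was well under one standard error. This stands. A reader might infer that the causal estimates will be biased; the documents give no information on what drives attendance and support only that they may be.

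**The sentence may compress two weights into one.** It does show an intention to deal with selection, and an unseen analysis plan may hold the detail. But the text presents selection adjustment as a consequence of balancing exposure, and the only covariate set it names is the confounder set. This is a stated rationale that is wrong, not detail left out.

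**Imputation may cover it.** Outcomes and predictors of missingness are to be in the imputations, which is good practice. The paragraph is limited to key variables where applicable and to intermediate time points, and age 21 is the last. It does not clearly reach members who do not attend, so it cannot be counted as the remedy. Nor does it show the reverse: a reader might infer that non-attenders' outcomes are assigned to imputation and weighting at once, but the article does not say that they will be imputed, and using the two methods for different gaps is routine.

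**Selection is acknowledged.** The comparison of included and non-included members, the stated limitation and the use of the age 10–11 measurements are real strengths. The comparison describes selection and does not correct it.

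**Deaths.** A reader might infer that children who died will be weighted back in. The article says only that attrition arose from mortality or loss to follow-up.

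**Conclusion.** Wrong as written, on a narrow point. The weights described address confounding only, and the claim that they thereby adjust for selection does not hold. Bias remains possible when attendance at 21 depends on the exposure and on causes of the outcome outside the confounder set. Its size and direction cannot be fixed from the documents: under assumed parameters the error ran from about nil to 0.55 mmHg upwards and 2.45 mmHg downwards.

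A reader might take 62% as the absent share. It holds only at the minimum target; the range is about 36% to 62% of live births, deaths included. At either end it is too large to rely on a method that does not act on it.

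The improvement seen with participation weights assumes that the predictors of attendance are measured and the participation model is right.

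**What to change.** Replace the weighting sentence under Objective 1 with two separate weights.

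1. Exposure weights, from a model of each exposure on the confounder set taken from its causal diagram.
2. Inverse-probability-of-participation weights, from a model of attendance at 21 fitted in cohort members not known to have died. Its predictors should include the exposure and the pregnancy, delivery and childhood variables already listed for the included versus non-included comparison. Where an exposure was measured only after some members had been lost, the model can be built in stages.

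Analyse with the product of the two, using robust or bootstrap standard errors. Add a sentence saying which gaps imputation covers and which the participation weights cover.

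Replace the statement that the estimates will be unbiased with the conditions under which they would be: no unmeasured confounding, and participation explained by measured predictors.

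The cost is one extra model on data already held, and somewhat wider intervals. Data collection does not change, and although the round is under way the wording can be corrected before outcomes are analysed.

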#### Objective 2: to assess (a) determinants of behavioural risk factors for CVDs, and (b) their associations with physiological determinants of CVDs in young Ugandan adults

For objective 2a, early-life and life-course predictors of behavioural risk factors such as tobacco use, alcohol use, physical inactivity and unhealthy diet will be explored. Logistic regression models will be used for tobacco and harmful alcohol use, and ordered logistic regression will be used to model levels of physical activity. To characterise the diet, principal components analysis will be applied to derive dietary patterns, and Least Absolute Shrinkage and Selection Operator models may also be used to improve robustness. For objective 2b, the behavioural risk factors will serve as exposures and physiological determinants as outcomes, analysed using linear regression.

### Objective 3: investigate nutritional and metabolic pathways through which early-life exposures may influence physiological determinants of CVDs

We will focus on both nutritional and metabolomics pathways. We will examine whether early-life growth influences micronutrient levels before age 5 years and whether these, alongside inflammation biomarkers, are associated with physiological risk markers at age 21 years. For metabolomics, we will analyse samples from individuals at the extremes of phenotypic expression. Metabolites will be identified and quantified using Progenesis QI software (Waters Corporation, Milford, MA, USA), and pathway-level analyses will be conducted using Integrated Molecular Pathway Level Analysis (IMPaLA). We will explore how early-life metabolic profiles relate to profiles at age 21 years and to extremes in exposure (eg, repeated *S. mansoni* infection vs none) and outcomes (eg, high vs low blood pressure). Causal mediation analysis will estimate both direct and indirect effects using a counterfactual framework, accounting for multiple mediators and applying sensitivity analyses to evaluate robustness to potential violations of confounding assumptions and measurement error.

Missing data will be assessed and handled using multiple imputation by chained equations when over 5% of data are missing for key variables, where applicable. Where repeated-measures data are available and intermediate data points are missing, we will use multiple imputation by chained equations to impute missing values, leveraging information from previous and subsequent measurements as well as relevant covariates. Therefore, imputations will include outcome variables and predictors of missingness, with 50 imputed datasets combined using Rubin’s rules.

### Ethics and dissemination

The study protocol has been reviewed and approved by the UVRI Research and Ethics Committee (UVRI REC Ref: GC/127/35), the Uganda National Council for Science and Technology (UNCST Ref: MV625), and the LSHTM Research Ethics Committee (LSHTM Ethics Ref: 8811). Any protocol amendments will be submitted for review and approval. Informed written consent will be obtained from all participants before study activities and will include provision and discussion of detailed information on what participation would involve, so that participants can make an informed decision based on their own perception of the risks and benefits. Participants will be compensated for their time and any incurred travel costs. For participants identified as having conditions that require long-term management, such as high BP or abnormal glucose or lipid levels, study clinicians will provide initial management and information on non-pharmacological management and refer to the hospital for further care. Participants identified as having conditions amenable to immediate management will be treated by the study clinicians. Focus group discussions carry the potential risk of confidentiality breaches if information is shared outside the groups. To mitigate this, we will continuously emphasise the importance of confidentiality to study participants throughout the study period.

Dissemination and stakeholder engagement are integral to the study design. Plans and findings will be shared and discussed with participants and community stakeholders through established engagement platforms, including participant advisory groups and locally appropriate communication channels. Results will be disseminated to the scientific community through peer-reviewed publications and conference presentations, and data will be made available to other researchers via established data-sharing platforms. Engagement with policymakers at district, national and international levels will facilitate translation of findings into policy-relevant outputs, with particular emphasis on informing NCD strategies in Uganda and the wider region.

## Data Availability

Data sharing not applicable as no datasets generated and/or analysed for this study.
